#### Randomization

The participants are randomized by the program Sealed Envelope (www.sealedenvelope.com) in an allocation ratio of 1:1 using block randomization. The block size is 6, 8, 10 participants per block and stratified according to the three chronic somatic conditions. Stratification is performed due to the strongly varying prevalence of chronic somatic conditions. Only RR, who is not involved otherwise in the trial process, will conduct the randomization process. AG, FL (study administration), and MM (statistical evaluation) are blinded and do not receive any information about the group allocation of study participants. The blinded members of the study team do not have access to documents showing group membership of participants.

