#### Guidance

The intervention is therapist-guided by e-Coaches, who report semi-standardized feedback after each completed module on the intervention platform to the participant using an e-Coach manual. The e-Coach manual is standardized to guarantee protocol adherence by the e-Coaches. e-Coaches are graduates of a Master’s Degree in Psychology or Pedagogy, who are enrolled in a training program in CBT with children and adolescents, closely supervised by licensed psychotherapists. The feedback content matches the participants’ tasks and is aimed to support adherence to treatment. The feedback also includes positive reinforcement to motivate participants to continue the intervention. For further questions, participants and e-Coaches can communicate via the intervention platform. e-Coaches will also send reminders to participants who do not complete intervention modules at the scheduled time via e-mail and telephone. The weekly schedule for processing a module is set by the participants themselves at the end of the previous module. In order to promote commitment, the intervention is blocked for the participant after three reminders without the participant reacting. For participants who indicate that they wish to continue, youthCOACH_CD_ will be reactivated. Table 2 shows the intervention structure and implementation.

**Table 2 Tab2:** Intervention structure, technical implementations, and support

Intervention structure	
• Seven weekly modules (50-70 min.)	
Implemented elements	
• Guidance by trained and supervised e-Coaches (graduates of a Master’s Degree, who are enrolled in a training program in CBT with children and adolescents)	
• One feedback message per module by e-Coaches	
• Reminders by the e-Coach if the modules are not processed at a date set in advance by the participant to promote adherence	
• Deactivation and reactivation when modules are not processed and three unsuccessful reminders	
• Answers to additional questions from e-Coaches and the study team	
• Tight security procedure for suicidal clues	
• Weekly challenges/ homework	
• Diaries via a mobile app with daily reminders	
• Information given by text and videos	
• Audio guided exercises	
• Patient examples written and presented as audio recordings	
• Metaphors, quizzes and conditional content	
• Modules can be repeated as often as desired	

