### Sample size/power calculation

A clinically significant effect of at least *d* = .50 for the mean difference between the groups is assumed, which refers to the severity of the primary outcome, i.e. a PHQ-ADS sum score [50] at 12 weeks post-randomization (t2). The assumption for the clinically significant effect is based on a meta-analysis by Ebert and colleagues, who reported a moderate to high effect size of *g* = .72 (95% confidence interval [CI] .55–.90) for Internet and computer-based CBT in the reduction of depressive and anxiety symptoms in youth [39], based on trials comparing Internet- and computer-based CBT to non-active control conditions (waitlist; placebo). However, given that TAU usually results in higher effect sizes compared to waitlist control groups, we regard a lower than *g* = .72 effect size as clinically relevant. The sample size calculation was carried out by an external statistician from the Department of Psychological Research Methods at Ulm University (MM) based on a power of .90 and α < .05 (two tailed) considering the cluster structure (intra-class correlation [ICC] = .02) of the different prevalence numbers of these chronic somatic conditions, resulting in 166 participants equally randomized to both conditions (2 × *n* = 83). According to a meta-analysis, studies evaluating the efficacy and effectiveness of computer-based psychological treatments for depression with therapeutic support reported a drop-out rate of approximately 28% [51]. For this reason, the sample is increased by 28%, resulting in a total of *N* = 212 participants (2 × *n* = 106).

Various measures will be taken to minimize study drop-outs. Participants receive €10 as an expense allowance at all psychometric assessment points. After successful completion of all assessments, participants can also take part in a prize draw. Moreover, in order to avoid drop-outs in the intervention group, youthCOACH_CD_ was designed to persuade the target group of AYA using e.g. multimedia features such as videos and audios as well as prompts and reminders [52].

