### Effectiveness analysis

There will be no interim evaluation of the primary outcome. All statistical analyses will be performed based on the intention-to-treat (ITT) principle. Additional per protocol analyses will be conducted in order to examine the effects of youthCOACH_CD_ in case of patients adhering to the intervention protocol. Participants who completed at least 80% of the intervention are defined as intervention completers (= per protocol).

The primary outcome will be analysed using a hierarchical linear model to account for clustering with the PHQ-ADS score at t2 as dependent variable and the baseline value as covariate, adjusting for sex, age, and chronic somatic condition. Standardized mean differences and 95% CIs will be calculated to measure the between-group effect size at post-treatment (t2) and follow-up (t3, t4). Secondary outcomes will be analysed accordingly.

Exploratory mediation and moderator analyses involving the primary and secondary outcomes as well as demographic data will be conducted. Moderator and subgroup analyses will be attempted in case of a sufficiently large sample size.

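### The only cluster level the article names is the three chronic conditions, already a covariate in the primary model; one-arm clustering by e-Coach is in neither the model nor the sample size

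*Protocol article*

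**What the plan says.** All references are to the protocol article.

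- *Effectiveness analysis*: the primary analysis is "a hierarchical linear model to account for clustering with the PHQ-ADS score at t2 as dependent variable and the baseline value as covariate". Sex, age and chronic somatic condition are further covariates. No grouping level is given for the hierarchical part.
- *Sample size/power calculation*: for d = .50, two-sided α of .05 and power .90, the calculation was made "considering the cluster structure (intra-class correlation [ICC] = .02) of the different prevalence numbers of these chronic somatic conditions". The stated requirement before drop-out is 166, that is 83 per arm. This is the only ICC in the article and the only place where a cluster level is named.
- *Randomization*: individuals are allocated 1:1 in blocks, "stratified according to the three chronic somatic conditions".
- *Guidance*: "The intervention is therapist-guided by e-Coaches". They give feedback after every module, answer questions and send reminders.
- *Therapeutic alliance*: the alliance with the e-Coach is measured in the intervention group only, so control participants have no e-Coach.

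**The concern.** Two things do not fit together.

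First, the model is said to handle clustering, but the one level the article identifies is a three-category factor that is also a fixed covariate. Once condition is a fixed effect, a random intercept for the same three groups has nothing left to estimate. A reader would believe that clustering had been dealt with when that term does no work.

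Second, there is a level at which outcomes may well be correlated. Participants guided by the same e-Coach share that person's style, responsiveness and skill. This happens in one arm only, which makes the design partially nested. An analysis that treats intervention participants as independent then understates the variance of the intervention mean. The primary p-value and confidence interval are at stake, and so is the power of .90 claimed in the sample size section and again in the Discussion.

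**Working it through.** **1. The plan's own figure.** Inputs from the sample size section: d = .50, two-sided α = .05, power .90.

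- Per arm without clustering: 2 × (1.960 + 1.2816)² / .50² = 84.06, so 85 (86 by the t-test).
- With a factor (1 − ICC): 84.06 × .98 = 82.4, rounded up to 83 per arm, 166 in total. This matches the stated figure exactly.
- With an ordinary cluster design effect over three clusters: 1 + (166/3 − 1) × .02 = 2.087, and 2 × 84.06 × 2.087 ≈ 351 in total. This does not match.

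The article gives no formula, so the .98 factor is an inference. It supports reading condition as the intended level. Since 83 is no more than the unclustered requirement, the figure contains no allowance for e-Coach clustering.

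**2. Condition as both fixed and random.** In 30 simulated trials with condition as a fixed covariate plus a random intercept, the random variance was not identifiable and the treatment standard error equalled that of ordinary ANCOVA (relative difference below 1e-14 in all 30). Randomisation is by individual within condition, so ANCOVA with the stratum as covariate is valid with respect to condition.

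**3. E-Coach clustering in one arm.** The article gives neither the number of e-Coaches (K) nor their ICC (ρ). Assumed: K from 4 to 20, ρ from .01 to .05, equal caseloads m = 83/K.

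- Intervention-arm variance factor: DE = 1 + (m − 1)ρ. The control arm has factor 1.
- True SE / planned SE = √((1 + DE)/2).
- Actual type I error = 2 × [1 − Φ(1.96 / SE ratio)].
- Power with the correct SE, level held at 5% = Φ(.50 / √((1 + DE)/83) − 1.96).

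Worked for K = 4, ρ = .05: m = 20.75; DE = 1 + 19.75 × .05 = 1.9875; SE ratio = √1.494 = 1.222; type I error = 2 × [1 − Φ(1.604)] = .109; power = Φ(2.635 − 1.96) = .750.

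| E-Coaches | ρ | SE ratio | Type I error | Power, no baseline adjustment |
|---|---|---|---|---|
| 20 | .01 | 1.008 | .052 | .892 |
| 20 | .05 | 1.039 | .059 | .873 |
| 8 | .02 | 1.046 | .061 | .869 |
| 8 | .05 | 1.111 | .078 | .826 |
| 4 | .02 | 1.094 | .073 | .837 |
| 4 | .05 | 1.222 | .109 | .750 |

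For comparison, 83 per arm with no clustering and no (1 − ICC) factor gives power .896. Simulation of the unclustered analysis at 83 per arm over the same range gave a type I error of about 5.3 to 11%, in line with the formula.

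The power column is for a test that uses the correct standard error. The uncorrected test would reject more often, but only because its level is above 5%. With very few e-Coaches, small-sample degrees of freedom would lower power somewhat further.

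**4. Effect of the baseline covariate on power.** Multiply the variance by (1 − r²), where r is the baseline-to-t2 correlation (not stated; assumed .3 or .5) and ρ refers to the residual variance. Over the same K and ρ, power is .92 to .79 at r = .3 and .96 to .86 at r = .5. At a given residual ICC the SE ratio is unchanged, so baseline adjustment can recover power but does not restore the 5% level.

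**The case against.** Several stronger readings are tempting, and the documents do not support them.

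- *The model accounts for no clustering.* The Effectiveness analysis section names no level. The trial is multicentre, so centre could be meant, and a full protocol or SAP may say so. What stands is that the article names condition and nothing else, and also adjusts for condition.
- *The ICC was applied in the wrong direction.* It was not shown to be. When individuals are randomised within strata and the analysis adjusts for stratum, between-stratum variance drops out of the treatment contrast. A factor of (1 − ICC) is then the right direction, and it changes the number only from 85 to 83 per arm. The fault is in calling strata clusters.
- *The confidence interval is too narrow.* This follows only if the e-Coach ICC exceeds zero. Feedback is semi-standardised, follows a standardised manual and is closely supervised, all of which may keep the ICC small. With 20 e-Coaches and an ICC of .01 the effect is negligible.
- *The trial is underpowered because of the e-Coaches.* The sample size text takes no credit for the baseline covariate, which may outweigh the loss.

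A practical objection also stands. The Randomization and Statistical analyses sections keep the statistician blinded, and an e-Coach code that exists in one arm only reveals allocation.

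None of this removes the point that the one-arm clustering built into the intervention is absent from both the model and the sample size.

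**Conclusion.** The point holds in a conditional form. If condition is the random level, that term duplicates a covariate and should go; the redundancy does not bias the treatment estimate or its standard error. The substantive gap is the e-Coach level. With an e-Coach ICC above zero, the planned standard error is too small: by about 1% of the true value at the mild end (1 − 1/1.008) and 18% at the other (1 − 1/1.222). That corresponds to a type I error of about 5 to 11% and, without baseline adjustment, power of about .89 to .75 at 83 per arm. These sizes rest on assumed values (4 to 20 e-Coaches, ICC .01 to .05, equal caseloads), because the article states none of them. The direction does not depend on those values; the size does. The matter is worth correcting because the remedy is cheap and concerns the primary analysis.

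**What to change.** 1. *Effectiveness analysis*: name the random level. Keep chronic condition as a fixed stratum effect only. If centre is intended, say so.
2. Assign an e-Coach to each intervention participant at allocation and log the e-Coach ID, so that participants who never start also have one under intention to treat.
3. Fit a partially nested model: the same covariates, a random e-Coach effect in the intervention arm only (each control as a singleton), and Kenward-Roger or Satterthwaite degrees of freedom. Make it the primary model, or at least a prespecified sensitivity analysis.
4. *Sample size/power calculation*: describe the conditions as strata, and state that 166 makes no allowance for e-Coach clustering.

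Costs: one logged variable, some rewording and slightly wider confidence intervals. With few e-Coaches the variance component will be imprecise. Because the e-Coach ID reveals allocation, the model should be scripted in advance and run either after the blinded analysis is complete or by a separate unblinded analyst.

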### Health economic evaluation

Cost-effectiveness analyses of the iCBT intervention will be estimated from the societal perspective by means of the net benefit method [94–96]. The incremental cost-effectiveness ratio (ICER) will be computed to estimate the maximum willingness to pay (MWTP) *λ* necessary for the gain of one QALY by iCBT in comparison to TAU+. The stochastic uncertainty of the ICER will be estimated by non-parametric bootstrapping [95, 96]. The interpretation of results is based on the cost-effectiveness acceptance curve using a range of MWTP thresholds between 0 and 100,000 € [95–97].

## Discussion

The aim of this study is to examine the (cost-)effectiveness of youthCOACH_CD_, an iCBT for AYA with a chronic somatic condition and comorbid depressive and/or anxiety symptoms.

The innovative aspects of the study are the following: (1) youthCOACH_CD_ is implemented directly into routine medical care. As such, the present study will provide important insights for health care policy on how to integrate iCBT into our health care systems. (2) Studies show that AYA between the ages of 12 and 25 spend an average of 22 h a week online with an increasing tendency to communicate, play, or entertain. Four out of five of 12- to 17-year-olds (80.6%) have used the Internet daily in the last 12 months [98]. Only 4.6% of adolescents at this age do not make use of the Internet. The fact that AYA grow up as digital natives could make online use of an intervention well accepted.

Continuing with advantages, the methodical strengths of the study are as follows: (3) The area-wide recruitment via the German patient registers enables a representative sample and facilitates generalization. (4) With a target sample of 212 adolescents, the study will be high-powered (1 – β = .90). (5) In addition to self-report questionnaires, the study also includes caregiver self-reports on their perception of participants’ conditions. This provides further insights into the effectiveness of iCBT. (6) Not only the effectiveness of youthCOACH_CD_, but also undesirable potential adverse events will be investigated in detail in this study. (7) As one of as yet only a few clinical trials on psychological interventions for AYA with chronic somatic conditions and symptoms of depression and anxiety, the present RCT also comprises cost-effectiveness analyses. (8) Finally, in addition to the psychological parameters, medical data are collected, which are linked to each other and thus allow deeper insights into comorbidity.

The study has several possible obstacles and limitations. First, adolescents aged 12 to 16 years need the informed consent of the custodial persons to participate in the study. This legal constraint might lead to a left-skewed age distribution of the study participants. By adjusting the covariate baseline to age, sex, and chronic somatic disease, this possible limitation is taken into account in the statistical analysis.

Second, intervention and study adherence might be limited in AYA, as has been reported before [99]. Therefore, a drop-out rate of 28% was established. As a counterstrategy we developed our intervention based on persuasive design aspects and provide it therapeutically guided—measures that are associated with improved intervention adherence [51, 100]. Additionally, participants receive a monetary compensation for their study efforts, which will likely increase study adherence.

Third, participant inclusion is based on depression/anxiety symptoms and not on mental disorder status. The reason for this is that the assessments are based on participants’ self-report, which is complemented by caregiver reports. Therefore, participants, caregivers, and physicians of the recruitment supporting clinics are informed that youthCOACH_CD_ is designed as a (guided) self-help intervention that does not replace on-site mental health care according to existing guidelines in case of manifest mental disorders.

Fourth, given the nature of the present trial, participants need to go through several self-report assessments. This might bias effectiveness results in two ways. On the one hand, the assessments might lead to a self-selection of participants with only those being randomized who are determined enough to finalize a comprehensive baseline assessment. At the same time, reminders on the follow-up assessments might have an intervention adherence facilitating effect, reminding participants not only to conduct the assessments but to continue the intervention or reminding them e.g. of learned intervention aspects. On the other hand, the comprehensive assessment with several self-report questionnaires might have a negative effect on trial adherence, increasing attrition rates. These not yet well examined and understood research biases on intervention effects inherent to RCTs need to be taken into account when interpreting the coming effectiveness findings.

In conclusion, Internet- and mobile-based interventions might have the potential to augment health care services substantially, as they could be a temporal and local flexible, accessible, and cost-effective treatment alternative. AYA with chronic somatic diseases and comorbid anxious and/or depressive symptoms could be supported by iCBT to reduce mental disturbances. With iCBT as a low-threshold and low-intensity intervention, progress and chronification of mental disorders might be preventable at an early stage. The first results of youthCOACH_CD_ are expected to be available in 2021.

### Trial status

Protocol version number 1.0 (submitted on 22/08/2019). Recruitment start is scheduled for October 2019 and will be expected to complete in April 2021.

## Data Availability

Individual participant data will be made available on request after de-identification beginning 12 months following article publication of the effectiveness and the cost-effectiveness paper. Data will be made available to researchers who provide a methodologically sound proposal, not already covered by others. Proposals should be directed to the corresponding author. Data requestors will need to sign a data access agreement. Provision of data is subject to data security regulations. Investigator support depends on available resources.

## Abbreviations

ATQ-R: Automatic Thoughts Questionnaire-Revised
AYA: Adolescents and young adults
BADS: Behavioral Activation for Depression Scale
BDI-II: Beck Depression Inventory-Revised
BSSS: Berlin Social Support Scales
CAMHSRI-DE: Child and Adolescent Mental Health Services Receipt Inventory
CATS: Child and Adolescent Trauma Screen
CBT: Cognitive behavioural therapy
COACH: *C*hronic C*o*nditions in *A*dolescents: Implementation and Evaluation of Patient-centred *C*ollaborative *H*ealthcare
CODI: Coping with a Disease (questionnaire for children and adolescents with chronic health conditions)
CSQ-I: Client Satisfaction Questionnaire adapted to Internet-based interventions
EQ-5D-Y: EuroQol Five-Dimensional Questionnaire-Youth
GAD-7: Generalized Anxiety Disorder Screener
GSE: General Self-Efficacy Scale
iCBT: Internet- and mobile-based cognitive behavioural therapy
ICC: Intra-class correlation
ICER: Incremental cost-effectiveness ratio
INEP-On: Inventory for recording negative effects of online interventions
ITT: Intention-to-treat
IUES: Internet-Use Expectancies Scale
MFQ: Mood and Feelings Questionnaire (caregiver)
PHQ-9: Patient Health Questionnaire
SCARED: Screen for Child Anxiety Related Emotional Disorders (caregiver)
SD: Standard Deviation
SRGS: Stress-Related Growth Scale
TAU+: Treatment as usual+
WAI-SR: Working Alliance Inventory-Short Revised
youthCOACH_CD_: youthCOACH_chronic disease_
